## Abstract

**Background:**

Illicit drug use has been rapidly increasing in South Korea, particularly among individuals in their 20s, contributing to a growing burden of substance use disorder (SUD). However, treatment infrastructure remains limited. Nationwide, only a small number of inpatient treatment hospitals are available, and treatment capacity in the Seoul metropolitan area is insufficient to meet growing demand. In addition, community-based addiction services are scarce, creating barriers to continuous care. Digital therapeutics (DTx) have emerged as a promising approach to improve treatment accessibility and continuity of care. In particular, cognitive behavioral therapy (CBT)–based DTx such as RESET-O, developed in the United States and authorized by the US Food and Drug Administration, have demonstrated clinical benefits in supporting addiction recovery. Building on this concept, our team developed D-STOP, a CBT-based DTx intervention designed to support individuals with SUD in the Korean clinical context.

**Objective:**

This study aims to evaluate the efficacy of D-STOP as an adjunctive DTx intervention for patients with SUD.

**Methods:**

This study is a randomized controlled clinical trial designed to evaluate the efficacy of D-STOP in individuals diagnosed with SUD. Following an initial screening assessment, 118 participants meeting the diagnostic criteria will be enrolled. Participants will be recruited from psychiatry departments at addiction treatment and clinical care institutions in Chuncheon, Seoul, Daegu, and Changnyeong, South Korea. During the 12-week intervention period, the experimental group will receive D-STOP in addition to treatment as usual, whereas the control group will receive treatment as usual alone. D-STOP delivers structured CBT-based modules and motivational enhancement interventions through a digital platform. During scheduled study visits, participants will also receive therapeutic feedback from psychiatrists or trained study staff. The primary end point is the abstinence success rate during weeks 9 to 12 of treatment. Logistic regression analysis will be used to estimate treatment effects and evaluate superiority compared with the control group.

**Results:**

The study protocol was approved by the institutional review board of Hallym University Chuncheon Sacred Heart Hospital on April 14, 2025. Funding began on April 1, 2023. Data collection started on August 4, 2025, and is expected to be completed by November 30, 2026. As of March 6, 2026, a total of 65 participants have been enrolled. An interim analysis of the primary efficacy outcome has been conducted based on the data available at the time of analysis; however, statistical significance has not been established due to the limited sample size. The final analysis is expected to be published in April 2027.

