### Data Analysis

All data collected in this trial will be analyzed based on the entire screened population. The number of participants excluded from the safety set and the reasons for exclusion will be reported relative to all enrolled participants. Exclusions from the full analysis set will be described relative to the safety set, and exclusions from the per-protocol set will be described relative to the full analysis set. The primary efficacy analysis will be conducted on the full analysis set according to the intention-to-treat principle.

Participants who discontinue the study prematurely (dropouts) will be included in the analysis in accordance with the intention-to-treat principle. Missing outcome data will not be imputed. If missing values occur in outcomes related to abstinence status, the participant will be considered as having failed (failure) for the purpose of analysis.

For efficacy analyses, the primary end point is the abstinence success rate during the final 4 weeks of the trial. This end point is intended to evaluate the efficacy of the DTx intervention in patients with SUD. Statistical significance will be assessed using multiple logistic regression analyses adjusting for stratification factors such as stimulant vs nonstimulant drug use and baseline abstinence status (abstinent vs nonabstinent) as covariates. The treatment effect will be expressed as the adjusted odds ratio for the experimental group relative to the control group along with 2-sided 95% CIs.

Superiority of the experimental group over the control group will be concluded if both of the following criteria are satisfied: (1) the 2-sided *P* value is less than .05, and (2) the lower bound of the 2-sided 95% CI for the adjusted odds ratio exceeds 1.0.

The secondary efficacy end points include (1) abstinence maintenance rate during the 12-week treatment period, (2) treatment retention rate during the 12-week treatment period, (3) total number of abstinent days, (4) longest duration of consecutive abstinent days, and (5) results from psychiatric and psychological assessment tools.

For these outcomes, multiple logistic regression analyses and analyses of covariance will be performed to compare differences between the experimental and control groups.

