### Ethical Considerations

This study was reviewed and approved by the institutional review board (IRB) of Hallym University Chuncheon Sacred Heart Hospital (CHUNCHEON 2025-03-004-004) and has been formally registered with the Clinical Research Information Service of the Korea Disease Control and Prevention Agency, a World Health Organization–recognized primary registry (registration KCT0010968).

The research team will provide each participant with a detailed explanation of the clinical procedures, expected treatment effects, and therapeutic services provided. This explanation will take approximately 30 minutes, after which written informed consent will be obtained. Participants will then receive access to the DTx app, followed by an orientation session on its use, which will also last approximately 30 minutes. Therefore, the total explanation and orientation period will be of approximately 1 hour.

During the course of the trial, each participant will be assigned a unique study identification number, which will be recorded in the electronic case report form for monitoring and data management purposes. All data collected during the study will remain confidential and will be securely stored in accordance with the IRB-approved protocol.

As the study involves no invasive procedures and the investigational DTx app is noninvasive, no serious risks are anticipated; therefore, no independent data monitoring committee has been established, as approved by the IRB. Nevertheless, internal investigators will continuously monitor participants’ treatment progress throughout the trial.

Participants enrolled in the D-STOP clinical trial will receive modest compensation for their participation. Compensation is provided at 3 time points across the 7 scheduled study visits (including the enrollment visit): at the baseline visit, the fifth visit, and the final seventh visit. Unlike the contingency management approach used in RESET-O, these incentives are not delivered immediately in response to treatment adherence or abstinence outcomes. Instead, they serve solely as nominal compensation for participation in the clinical study. Each compensation is KRW 50,000 (US $35) per visit, and participants will receive a total compensation of KRW 150,000 (US $105).

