## Results

The study has been funded for a 3-year period starting on April 1, 2023. This study has progressed to the initiation of the confirmatory clinical trial following approval from the Ministry of Food and Drug Safety and an IRB amendment review at Hallym University Chuncheon Sacred Heart Hospital in April 2025. Data collection began on August 4, 2025, and is expected to be completed by November 30, 2026. As of March 6, 2026, a total of 65 patients have been enrolled, and an interim analysis has been conducted based on the data available at the time of analysis. However, statistical significance could not be established due to the limited sample size. A final analysis will be conducted once all data have been collected, and the results are expected to be reported in spring 2027.

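### The article reports a mid-trial significance test of the primary outcome that its analysis section does not describe, while the final test keeps the full two-sided .05, so the 5% error level is not assured as written

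*Protocol article*

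**What the plan says.** The abstract's Results paragraph reports: "An interim analysis of the primary efficacy outcome has been conducted based on the data available at the time of analysis". It adds that "statistical significance has not been established due to the limited sample size". The Results section of the main text repeats that "an interim analysis has been conducted based on the data available at the time of analysis" and that "statistical significance could not be established due to the limited sample size". Both places give 65 enrolled as of 6 March 2026, data collection from 4 August 2025 to an expected end on 30 November 2026, and a final analysis still to come. The Methods paragraph of the abstract gives the target: "118 participants meeting the diagnostic criteria will be enrolled".

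The Data Analysis section sets one success rule for the primary end point, on the adjusted odds ratio. The two-sided P "value is less than .05, and (2) the lower bound of the 2-sided 95% CI for the adjusted odds ratio exceeds 1.0". It mentions no interim analysis, boundary or allocation of alpha.

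Three other statements bear on the point. The Aim section calls the trial confirmatory, the Design section calls it open label, and Ethical Considerations says that "no independent data monitoring committee has been established" and that internal investigators follow participants' progress. The primary outcome section requires both negative urine screens and a self-report of no drug use, recorded in the app in one arm and on paper in the other.

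**The concern.** Two statements in one article do not fit together. The Results describe a comparison of the primary outcome judged against statistical significance while the trial was still recruiting. The Data Analysis section is written as if the final test were the only one, and gives it the whole .05.

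Two things are at stake. The first is the type I error of a confirmatory superiority claim: two chances to claim success at .05 do not add up to a 5% procedure. The second is trial conduct. Up to 118 − 65 = 53 participants were still to be enrolled at 6 March 2026. Staff and participants know the allocation, part of the end point is self-reported, and no independent body is described that would keep a comparative result away from the people running the trial. Access to that result could influence encouragement and recording, and any later amendment could be challenged as data-driven.

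**Working it through.** **Inputs from the article.** Planned N = 118; enrolled by 6 March 2026 = 65; first data collection 4 August 2025; end point covers weeks 9–12; Table 1 places enrolment at week −4 and baseline at week 0; final rule two-sided P<.05 with the lower 95% limit above 1.0.

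**The plan's own figure.** One test at |Z| > 1.96 gives 2 × (1 − Φ(1.96)) = 0.0500. The confidence-interval criterion allows success only in the favourable direction, so a false claim of superiority has probability 0.025. With a single look, the stated rule is exact.

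**Information fraction t (not stated).**
- Ceiling: 65/118 = 0.55, if every enrolled participant had an outcome.
- Assuming uniform accrual, 4 August 2025 to 6 March 2026 is 214 days, or 65/214 = 0.304 participants per day.
- With an 84-day lag (counting from week 0): 0.304 × (214 − 84) ≈ 39, so t = 39/118 = 0.33.
- With a 112-day lag (counting from week −4): 0.304 × (214 − 112) ≈ 31, so t = 31/118 = 0.26.

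**Overall error if both looks could claim success at .05.** The two Z statistics are treated as bivariate normal with correlation √t. Overall error = 0.05 + 0.05 − P(both |Z| > 1.96).

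| t | √t | P(both) | Overall, two-sided | Favourable direction |
|---|---|---|---|---|
| 0.26 | 0.51 | 0.0095 | 0.0905 | 0.045 |
| 0.33 | 0.57 | 0.0116 | 0.0884 | 0.044 |
| 0.55 | 0.74 | 0.0186 | 0.0814 | 0.041 |

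An earlier look with fewer outcomes gives a higher figure (0.093 at t = 0.17). The limit for independent tests is 1 − 0.95² = 0.0975.

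**Overall error in other cases.**
- No success claim possible at the interim: the final test is the only route to a claim, and the error stays at 0.0500.
- O'Brien-Fleming-type spending for t = 0.26 to 0.55: interim level about 0.00002 to 0.005, final level 0.0500 to 0.0484. Keeping .05 at the end would then add very little.
- Haybittle-Peto, interim level .001: the final level that holds the overall error at 0.05 is 0.0494 (t = 0.26), 0.0495 (t = 0.33) or 0.0498 (t = 0.55). A final level of .049 lies below all three.

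**The case against.** The strongest reply is that this is a condensed article. Interim timing, boundary and purpose are commonly left to the full protocol or the analysis plan, and neither is shown. That stands. A reader might infer that the look was unplanned, that it was tested at .05 and that nothing was charged for it, but no sentence says so.

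A reader might also infer that the 5% level has already been broken. That does not follow. The 8–9% figure needs a nominal interim level of .05 and the option of claiming success on it. The article describes no early-stopping or early-claim rule and says that a final analysis will follow once all data are in, which fits a look without decision power. Saying that significance was not established describes a result; it does not show that a claim would have been made had it been reached.

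Nor do the documents show that site investigators know the direction of the effect. Only non-significance is disclosed, with no estimate, rate or P value, and nothing says who saw results by arm. Self-report is entered by participants and is paired with a urine screen, so the conduct risk is a possibility and not a documented event.

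Brevity does not dispose of the point, however. The article states a final rule, and it also reports a significance test on the same outcome that the rule leaves out. If alpha was allocated to the look, the stated final level may need to change, though hardly at all under a very conservative boundary. If none was, the basis for keeping .05 is that no claim was possible, and that has to be stated.

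**Conclusion.** The point holds in conditional form: the two-sided 5% level is not assured as written. The overall error is about 8.1% to 9.1% two-sided, or 4.1% to 4.5% in the favourable direction against 2.5%, if a significant interim result at .05 could have supported a superiority claim. It is 5% if no claim was possible, and very close to 5% under a conservative boundary. The document does not say which case applies.

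The range rests on t between 0.26 and 0.55. The upper value follows from the enrolment count; the lower values assume uniform accrual. The conduct risk is separate from the alpha question and applies in every case unless access to arm-level results was restricted. The matter needs settling before the final data are seen, because a statement about the look's status made afterwards would carry little weight.

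**What to change.** Before database lock:

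1. Amend the Data Analysis section to record the look: whether it was prespecified, its threshold and purpose, the number of participants with week-12 outcomes, who saw results by arm, and that no design change followed (if that is so).
2. State the consequence for the final test.
   - If there was a prespecified boundary, state it and use the matching final level and confidence interval.
   - If it can be documented that the look could not lead to a success claim, either say so and keep .05, or conservatively charge a nominal .001 (Haybittle-Peto) and test the final at about P<.049 with a 95.1% interval in the second criterion.
   - If a claim at .05 was possible, state that strict 5% control cannot be restored, and report the overall error at the actual information fraction.
3. Take no further comparative looks, and withhold arm-level results from site staff until lock.

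A Pocock-type final level chosen now would not repair a look taken at .05. Such spending presumes interim levels of about .018, .022 or .033 (t = 0.26, 0.33, 0.55), and a look at .05 with a claim available has already used the whole 5%.

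The cost is an amendment and wording. On the Haybittle-Peto route the final threshold falls by at most about .001, and no extra participants are needed.

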**Conclusions:**

DTx have the potential to expand access to evidence-based addiction treatment in resource-constrained settings. This study will provide clinical evidence on the efficacy and feasibility of D-STOP as a digital treatment support tool for patients with SUD.

## Introduction

In South Korea, the spread of narcotics has been accelerating. In particular, the proportion of overdose cases among individuals in their 20s has increased markedly over the past several years, accounting for more than 30% of all identified cases and representing the largest affected age group. Among young adults with mental health problems, a concerning cycle has emerged in which individuals seek psychotropic substances and subsequently engage in repeated misuse. As a result, many addiction specialists have emphasized the urgent need for comprehensive measures to promote treatment engagement and prevent relapse, including policy initiatives, expansion of treatment services, and the development of recovery and rehabilitation programs [1].

Despite the increasing prevalence of substance use disorder (SUD), treatment infrastructure in South Korea remains limited. Only a small number of hospitals provide specialized inpatient treatment for individuals with SUD, and access to intensive treatment programs is restricted in many regions [2]. In the Seoul metropolitan area, where a large proportion of drug-related crime occurs, the availability of treatment facilities remains insufficient to meet the growing demand. Furthermore, community-based addiction services remain underdeveloped, limiting opportunities for continuous treatment and long-term recovery support [3]. Social stigma associated with drug use also creates additional barriers to care, discouraging individuals from seeking treatment and contributing to delayed intervention [4].

The challenges surrounding addiction treatment are not unique to South Korea. There is international evidence suggesting that a large proportion of individuals with SUD do not receive adequate treatment. For example, national survey data from the United States indicate that many individuals with SUD do not access treatment services due to structural barriers such as limited treatment availability, financial constraints, or lack of motivation for treatment engagement [5]. In addition, structural inequalities in health care systems may further restrict access to addiction treatment and medication-assisted therapy in socially disadvantaged communities [6].

Psychosocial interventions remain the cornerstone of treatment for SUD. Among these approaches, cognitive behavioral therapy (CBT) has consistently demonstrated effectiveness in reducing substance use and preventing relapse across numerous clinical trials and meta-analytic studies [7-10]. CBT focuses on identifying maladaptive cognitive patterns and behavioral triggers associated with substance use while strengthening the coping strategies and self-regulation skills necessary for sustained recovery [11,12].

In addition to CBT, motivational enhancement therapy (MET) and motivational interviewing techniques are widely used to address ambivalence toward behavior change in patients with addiction [13,14]. These approaches aim to strengthen individuals’ intrinsic motivation for recovery and improve engagement in treatment. Previous studies have shown that motivational interviewing can significantly enhance readiness for change and treatment adherence, particularly during the early stages of addiction treatment [15,16].

More recently, mindfulness-based interventions have been introduced as complementary approaches for managing craving and emotional dysregulation associated with SUD [17]. Mindfulness-based relapse prevention programs aim to increase awareness of craving, emotional distress, and automatic behavioral responses related to substance use [18]. There is evidence suggesting that mindfulness-based interventions can reduce relapse risk by improving emotional regulation and attentional control, thereby enabling individuals to respond more adaptively to craving and stress-related triggers [19].

In addition, stress management and relaxation-based interventions have been incorporated into addiction treatment programs to address the role of stress in relapse vulnerability. Stress exposure has long been recognized as a critical factor contributing to craving and relapse among individuals with substance dependence. Techniques such as breathing training, progressive muscle relaxation, and guided relaxation exercises may reduce physiological arousal and improve coping responses to stress-related triggers [20,21].

Digital therapeutics (DTx) have emerged as promising tools for delivering evidence-based behavioral interventions at scale, particularly in areas where access to specialized addiction treatment services is limited. Advances in digital health technologies have recently enabled these evidence-based psychological interventions to be delivered through DTx platforms. DTx provide structured behavioral treatment through software-based programs that can be accessed remotely, allowing patients to engage in therapeutic interventions outside traditional clinical settings. Such approaches have the potential to improve treatment accessibility, enhance continuity of care, and reduce barriers related to stigma or geographical limitations [22,23].

One example is RESET-O, a prescription DTx intervention authorized by the US Food and Drug Administration for the treatment of SUD [24]. The effectiveness of digital behavioral interventions for SUD has also been supported by randomized controlled trials evaluating internet-delivered treatments [25].

Building on these treatments, our research team developed D-STOP, a CBT-based DTx intervention designed to support individuals with SUD in South Korea. In addition to CBT-based treatment modules, D-STOP incorporates complementary psychological strategies, including motivational enhancement, mindfulness-based coping techniques, psychoeducation, and crisis de-escalation strategies.

This study evaluates the efficacy, validity, and acceptability of D-STOP as a DTx intervention for individuals with SUD. By enabling patients to engage in structured behavioral treatment remotely, the intervention may help overcome barriers related to stigma, limited treatment access, and insufficient treatment infrastructure in South Korea.

## Methods

### Aim

The primary objective of this confirmatory clinical trial is to evaluate the feasibility, therapeutic efficacy, and acceptability of a CBT-based DTx intervention (D-STOP) within Korean health care settings. Feasibility and efficacy will be assessed by determining whether the use of D-STOP, administered as an adjunct to treatment as usual (TAU) for patients with SUD, leads to improvement in addiction-related symptoms.

### Design

Using a prospective design, we will collect longitudinal data on patients with SUD for subsequent analysis. Participants will be assigned in a 1:1 randomized fashion to a control group (TAU) or an experimental group (TAU+D-STOP). The trial will be conducted in an open-label manner. The primary aim is to demonstrate the superiority of the experimental arm over the control arm in treatment efficacy. Outcomes will be derived by integrating quantitative and qualitative data sources, including measures captured within the D-STOP app and standardized diagnostic and assessment instruments.

The meaning and implementation of TAU may vary across different medical specialties. In this study, TAU refers to maintaining the medications and treatment approaches that participants were receiving prior to enrollment in the clinical trial. With respect to medications, participants are allowed to reduce the dosage or discontinue previously prescribed medications during the study period; however, increasing the dosage or introducing new medications is not permitted.

Regarding psychosocial treatments, participants engaged in psychosocial intervention programs prior to enrollment (eg, Narcotics Anonymous meetings or 12-step addiction recovery programs) are allowed to continue participating in them. However, the initiation date of the psychosocial treatment program is required to precede the start date of participation in this clinical trial. To minimize potential confounding effects, preference is given to enrolling individuals who are not actively participating in such programs.

In addition, TAU in this study is limited to patients receiving outpatient care only. During the clinical trial period, the total number of hospital visits is scheduled to be 7. If a participant receiving outpatient care requires hospitalization during the trial period, this is considered a relapse-related event and recorded as a notable clinical occurrence; however, such cases are not classified as study withdrawal.

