#### Procedures

This clinical trial is currently in the recruitment phase. Recruitment strategies include conducting screening tests for patients with SUD who present at 1 of the 4 participating regional medical institutions. Eligibility will be determined based on the inclusion and exclusion criteria described above, and suitable participants will be enrolled. Additional recruitment will be carried out through community organizations (eg, the Seoul branch of the Korea Association Against Drug Abuse) using external advertisements.

During the 12-week trial period, participants will be required to attend 7 visits. At each visit, the following will be assessed: (1) abstinence status within the app, (2) treatment adherence, (3) diagnostic assessments for secondary end points, and (4) urine drug screens and pregnancy tests.

If drug relapse is detected through urine testing or through abstinence status recorded on the app during weeks 1 to 8, the participant will continue in the clinical trial. However, relapse occurring during weeks 9 to 12, which correspond to the assessment period for the primary end point, will be considered treatment failure.

With respect to treatment adherence, if participants use less than 35% of the app’s therapeutic services, the study psychiatrist or clinical research coordinator will encourage them to improve their engagement.

Upon enrollment, participants will be provided with the DTx app. Over the course of the 12-week self-management program, they will complete 17 modules accessible via the app: 6 treatment modules, 4 emergency modules, 1 daily life management module (via a calendar), and 6 relaxation training modules.

Throughout the trial, adverse events will be monitored. If an adverse event occurs, it will be documented in the adverse event log and reported to the study sponsor within 24 hours via the rapid adverse event reporting system.

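### The Design section labels every hospitalization relapse-related whatever its cause, under a category that is never tied to the adverse event rule in Procedures

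*Protocol article*

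**What the plan says.** The Design section limits treatment as usual to outpatient care and then covers the participant who is admitted. If someone has to be hospitalized while on trial, "this is considered a relapse-related event and recorded as a notable clinical occurrence; however, such cases are not classified as study withdrawal".

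The safety rule is in Procedures: "Throughout the trial, adverse events will be monitored", and "If an adverse event occurs, it will be documented in the adverse event log and reported to the study sponsor within 24 hours". Table 1 schedules adverse event monitoring at visits 2 to 7. Neither place makes an exception for hospitalization or relapse.

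Two other parts matter. Procedures makes relapse in weeks 9 to 12 a treatment failure. Ethical Considerations states that "no serious risks are anticipated; therefore, no independent data monitoring committee has been established", and adds that internal investigators will keep watch on participants' progress throughout.

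**The concern.** The Design sentence assigns a cause before anyone has looked for one. Taken literally, an admission for an injury, an infection or a psychiatric crisis without drug use is relapse-related on the day it happens. Hospitalization is also the only event of a serious kind that the article names for participants on trial, so this rule governs the events that matter most for safety.

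Three things are at stake:

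- **Cause.** A table of admissions built on this label could not separate relapse from anything else, in either arm.
- **Completeness of the log.** A coordinator has one specific instruction for admissions and one general instruction for adverse events, and nothing says that both apply. Sites may settle this differently. Because the trial is open-label, they may also settle it differently by arm.
- **The primary end point.** If a relapse in weeks 9 to 12 is a failure and an admission is by definition relapse-related, a site might score the admission itself as a failure.

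There is no independent data monitoring committee, so the investigators and the sponsor's reporting route carry the safety oversight that the article describes. That makes a clear rule more valuable.

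**Working it through.** No arithmetic applies. The question is how the sections read together.

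**Step 1: is the label conditional on cause?** The Design sentence has one trigger, the need for hospitalization in someone receiving outpatient care. It names no cause, no assessment and no exception. The automatic attribution is therefore in the text and is not inferred from silence.

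**Step 2: is the category linked to the adverse event log?** *Notable clinical occurrence* appears once, in Design. Procedures, Table 1, Data Analysis and Ethical Considerations do not use it. Design gives it no form, reporting time or recipient. Procedures gives adverse events all three: "it will be documented in the adverse event log and reported to the study sponsor within 24 hours via the rapid adverse event reporting system".

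**Step 3: does Design exempt admissions from the log?** No. It does not say that its record replaces an adverse event entry, and the Procedures rule has no carve-out. Both records can be kept for the same admission. The text leaves room for a site to keep only one, but does not tell it to.

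**Step 4: can the label change the primary outcome?** Outcome Measures defines success by negative urine screens plus self-reported non-use throughout the final 4 weeks. Hospitalization is not part of that definition. In Procedures, the sentence on weeks 1 to 8 names the means of detecting relapse (urine test or app record). The next sentence, on weeks 9 to 12, says only that relapse is a failure. For a participant admitted in weeks 9 to 12 there are three cases:

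| Abstinence data in weeks 9 to 12 | Result without the label | Could the label change it? |
|---|---|---|
| A positive urine screen or reported use | Failure | No |
| Abstinence data missing | Failure, under the missing-data rule in Data Analysis | No |
| Complete, all negative | Success, under Outcome Measures | Yes, if *relapse-related* is read as relapse |

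The ambiguity is confined to the third row: an admitted participant with a complete and clean record.

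**Step 5: can the effect be sized?** The article plans 118 participants and reports 65 enrolled as of March 6, 2026. It gives no number or rate of admissions and does not say whether any has occurred. A count of serious events lost from the log would need an assumed admission rate and the further assumption that no admission reaches the log. Step 3 shows that the text does not support the second assumption, so no figure is offered.

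**The case against.** The strongest reply is that the sentence is not a safety rule. It sits in the paragraph that restricts treatment as usual to outpatients, and it answers what happens when someone leaves that setting: the event is noted and the participant stays in the study. Elsewhere the article discusses inpatient care as addiction treatment, so the authors may have had only admissions for substance use in mind. The safety rule is unconditional and stands in Procedures. Definitions of seriousness, causality assessment and the forms themselves normally belong to the full protocol, which is not shown, and their absence from an article is no defect.

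Much of this stands. A reader might infer that hospitalizations are diverted from adverse event reporting, that serious events will be undercounted, or that non-relapse admissions will be counted as relapses in the efficacy analysis. The documents do not support any of these. Nothing removes admissions from the log, no outcome definition counts hospitalization as relapse, and the statement about serious risks is an expectation based on a noninvasive product, not a conclusion drawn from event counts.

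The defence does not reach the attribution itself. Silence may be left to the full protocol, but this is a stated rule, and it assigns one cause to every admission. If the authors meant only admissions for drug use, the sentence does not say so.

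A separate tension is rightly pointed out. Design says that an admitted participant is not withdrawn, while Participants treats a visit missed outside its window of 5 days either side as discontinuation. Those passages also need reconciling, but the present point does not depend on them.

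**Conclusion.** The point holds in a limited form. The Design section attributes every hospitalization to relapse regardless of cause and files it under a category not connected to the adverse event rule. Followed as written, unrelated admissions would be misattributed. Some might be missed from the adverse event log if a site reads Design as the specific rule. Whether the label alone makes an admission in weeks 9 to 12 a treatment failure is left open, but this could matter only for participants whose abstinence record for those weeks is complete and negative.

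The misattribution rests on the wording alone. The possible omission from the log rests on an assumption about how sites read two unreconciled sections, and the full protocol may already settle it. The size is unknown. This is a should-fix matter of clarity in safety recording. It is not evidence that safety reporting has failed or that the primary analysis is biased.

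**What to change.** Reconcile Design and Procedures:

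1. Remove the automatic attribution. Record the documented cause of each admission, and apply *relapse-related* only where that cause is drug use.
2. State that hospitalizations also go through the adverse event log and the 24-hour report to the sponsor, whatever other record is kept.
3. State that the label alone does not determine the primary end point, which continues to follow the urine screens, self-report and missing-data rule.
4. Check any admissions recorded since data collection began on August 4, 2025, for documented cause and for an entry in the log. This does not presume that any occurred or were misfiled.
5. Tabulate admissions by arm and by cause in the final report.

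The cost is a short wording amendment, a cause field on the case report form if there is none, and a brief look back over the participants enrolled so far. The reported number of adverse events may rise. Sample size, randomization and the primary analysis model do not change.
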